### Safety

Since the intervention is not a classic patient-directed intervention but rather a health consultation, there are no intervention-related SAEs or AEs that need to be reported. However, hospitalizations will be recorded during visits and telephone visits. As these hospitalizations cannot be directly related to the intervention, they will not be classified as AEs or SAEs.

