#### Intervention group

The participants in the intervention group will receive access to the same app in addition to standard care. In addition to the standard functions, users can connect the app to the university hospital, allowing vital signs and blood parameters to be displayed directly within the hospital’s system. Participants in the intervention group will also complete a 7-day nutrition and activity log. Personalized nutrition and exercise recommendations are provided on the basis of this log, the results of the baseline assessment, and the blood and vital parameters transmitted through the app. Individualized training plans for exercise, consisting of endurance training guidelines and exercises for resistance and balance training, will be provided to patients. The recommendations are based on the WHO guidelines on physical activity, which include: aerobic exercise for at least 150 min per week at moderate intensity, resistance training twice per week, and balance training twice per week [25]. For nutrition, recommendations tailored to the patient’s goals (weight reduction, weight gain, improvement of blood values, etc.) and easily integrable into daily life will be given.

This individualized care aims to counteract the reduction in physical performance and promote the optimization of body composition. In addition, participants in the intervention group will undergo a 3-week inpatient rehabilitation program, during which they will receive intensive care from physicians, physiotherapists, occupational therapists, sports therapists, psychologists, and nutritionists. The rehabilitation takes place between Visit 2 and Visit 3, as sufficient time must be allocated for the application process and participant preparation. The rehabilitation clinic has confirmed in advance that adequate capacity is available to accommodate participants in the intervention group.

Regular telephone check-ins (every 2 months) will be conducted to monitor and potentially adjust the recommendations between visits. During these telephone check-ins, general well-being is assessed, and adherence to or difficulties with the recommendations are discussed. Study participants are informed about these contacts on the day of enrollment. Regular contact is intended to ensure adherence to the implementation of recommendations as well as compliance with scheduled visits.

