**Fig. 1 Fig1:**
[figure not shown]
Study timeline (Created in BioRender. [name] (2025) https://BioRender.com/f20g408)

**Table 1 Tab1:** Participant timeline

	Study period			
	Enrollment	Allocation	Post-allocation	
Timepoint	0	0	t_1_	t_2_
Eligibility screen	X			
Informed consent	X			
Allocation		X		
Interventions:				
Intervention group			X	X
Control group			X	X
Assessments:				
Body composition Body mass index Skeletal muscle mass Body fat mass Waist circumference	X		X	X
Physical performance 6-min walking test Sit-to-stand test (60 s) One-legged stance test Timed up and go test Stair climbing test	X		X	X
Frailty	X		X	X
Questionnaires Freiburg Physical Activity Questionnaire Barthel Index KDQOL	X		X	X
Blood parameters	X		X	X
Bone density	X			X

An interim analysis is planned at approximately the midpoint of the overall study duration (after one and a half year). However, this analysis will serve only internal monitoring purposes (e.g., assessment of feasibility, recruitment, and data quality) and is not intended to inform early termination of the study based on efficacy, harm, or futility. A termination of the study based on these results is not anticipated.

The University Hospital Erlangen is, however, obligated to notify the funder if it becomes evident that the research project can no longer be feasibly implemented. In such a case, any decision to discontinue the study prematurely will require prior agreement between the study leadership and the sponsor. No other circumstances could lead to study termination.

Any amendment to the study protocol that may impact the conduct of the study, the potential benefit to the patient, or patient safety, including changes to study objectives, study design, patient population, sample size, study procedures, or significant administrative aspects, requires a formal amendment to the protocol. Such an amendment must first be discussed by the principal investigator with the funder before submission to the ethics committee. Upon approval by the ethics committee, the amendments are then recorded in the trial registries. At this time, no protocol amendments are planned.

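### The Safety section rules out intervention-related events in advance, contrary to the protocol's own description of the intervention; hospitalizations also appear to be asked about more often in the intervention arm

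*Protocol article*

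**What the plan says.** The Safety section gives a premise, a rule and one data source.

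- Premise: "Since the intervention is not a classic patient-directed intervention but rather a health consultation".
- Rule: "there are no intervention-related SAEs or AEs that need to be reported".
- Data source: "However, hospitalizations will be recorded during visits and telephone visits".
- Status of those data: "As these hospitalizations cannot be directly related to the intervention, they will not be classified as AEs or SAEs".

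The Intervention group section describes individual training plans (endurance, resistance, balance), nutrition advice aimed at goals such as losing or gaining weight, and an inpatient stay: "participants in the intervention group will undergo a 3-week inpatient rehabilitation program". It is also the only place where telephone contact is described: "Regular telephone check-ins (every 2 months) will be conducted to monitor and potentially adjust the recommendations between visits". The Control group section mentions no calls, and the Study design overview says that controls receive the app alone. Study visits at 0, 6 and 12 months apply to both arms.

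After Table 1, the article says that the interim analysis is not meant to inform stopping for harm. It names infeasibility as the ground for early discontinuation and adds: "No other circumstances could lead to study termination".

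**The concern.** Whether an event is related to an intervention is judged event by event. Here it is decided for all participants by a definition, and the definition does not match the intervention described elsewhere in the article. The Conclusions section promises to say whether the care is beneficial. If a report then states that no intervention-related event occurred, that statement will carry no information, because no other result was possible.

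The second issue is ascertainment. If one arm is asked about admissions every two months and the other every six, equal true rates can show up as unequal recorded rates. The rehabilitation stay, planned for the intervention arm only, is itself an inpatient admission, and the Safety section does not say whether it counts.

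**Working it through.** **Step 1. The causality rule against the rest of the article.** No arithmetic applies.

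| Safety section | Elsewhere in the protocol article |
|---|---|
| The intervention is a consultation | Intervention group: individual endurance, resistance and balance training, tailored nutrition, 3 weeks of inpatient rehabilitation |
| No intervention-related event needs reporting | Selection criteria: users of walkers and wheelchairs are eligible. Study design overview: geriatric rehabilitation is foreseen for some participants |
| Hospitalizations cannot be directly related | Background: a 12-month exercise trial in end-stage renal disease (n = 1211) is cited as reducing morbidity measured by hospitalizations |

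The third row is the sharpest contradiction. If exercise can lower hospitalization in the rationale, a link between the intervention and hospitalization cannot be excluded in the Safety section.

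**Step 2. Enquiry points over 12 months.** Visits after baseline fall at months 6 and 12 in both arms. Calls are two-monthly. Assuming they fall between visits, they come at about months 2, 4, 8 and 10.

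- Control: 2 visits = 2, with a recall interval of 6 months.
- Intervention: 2 visits + 4 calls = 6, with a recall interval of about 2 months.

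**Step 3. Possible size of the tilt.** The article gives no recall data, so everything here is assumption. True rates are taken as equal in both arms.

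(a) Assumed capture of 95% with 2-month recall and 70–90% with 6-month recall. The spurious rate ratio is the quotient:

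- 0.95 / 0.90 = 1.06
- 0.95 / 0.80 = 1.19
- 0.95 / 0.70 = 1.36

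(b) Assumed constant forgetting rate m per month. The share recalled over an interval of L months is (1 − exp(−mL)) / (mL).

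| m per month | Control, L = 6 | Intervention, L = 2 | Ratio |
|---|---|---|---|
| 0.01 | 0.971 | 0.990 | 1.020 |
| 0.03 | 0.915 | 0.971 | 1.061 |
| 0.05 | 0.864 | 0.952 | 1.101 |
| 0.10 | 0.752 | 0.906 | 1.205 |

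Together the two models span about 1.02 to 1.36. The direction is the same throughout (against the intervention); the size is not known.

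**Step 4. Effect of using common visits only.** Enquiry points become 2 against 2 with equal recall intervals, and the scheduled imbalance disappears.

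**Step 5. What can still be collected.** Recruitment ran from 18.09.2023 to 30.06.2025, and the current version is dated 30.07.2025. On that date, participants enrolled before about 30.07.2024 were due to have finished 12 months, and those enrolled before about 30.01.2025 were due to have passed month 6. The last 12-month visits fall around 30.06.2026.

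**The case against.** Several stronger readings are tempting, and the article does not support them.

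- *Control hospitalizations go unrecorded.* They do not: they are recorded at visits, which both arms attend. The imbalance lies in the additional calls.
- *Controls receive no calls.* This is a strong inference from the Study design overview and the two group descriptions. It is not stated outright, and the full protocol is not shown.
- *The trial cannot detect harm.* This is too broad. Death is captured as an end state, and waiting-list status is an outcome. Potassium, phosphate, calcium, creatine kinase and C-reactive protein, together with frailty and physical performance, are measured in both arms. Patients with conditions that prohibit physical activity are excluded. What is lost is the assessment of relatedness, along with falls and injuries that do not lead to admission.
- *A biased safety comparison is planned.* Hospitalization is not a listed outcome, and no between-arm analysis of it is stated. The tilt would arise only if such a table were made from all sources.
- *The ratio has been estimated.* It has not. At the low end of the assumed range it is negligible.

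One could also read the word directly as conceding only that attribution is difficult. That does not rescue the rule: difficulty is a reason to assess each case, and the section still excludes every hospitalization from classification and says that no related event needs reporting.

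These points narrow the concern considerably. They leave the causality rule untouched, because it is an explicit statement with a stated reason. It cannot be put down to detail omitted from a condensed article.

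**Conclusion.** The main point holds on the text alone and needs no assumption. The Safety section excludes related events and any causal link for hospitalizations in advance, and this contradicts the article's description of the intervention, its eligibility criteria and its own rationale. Related events are therefore zero by definition, and the section makes no provision for recording falls or injuries without admission.

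Unequal ascertainment is secondary. It rests on the inference that controls are not telephoned and on calls falling between visits (about 6 enquiry points against 2). A comparison using all sources would lean against the intervention. The article does not allow the amount to be estimated; 1.02 to 1.36 is an illustration under assumed recall only. Neither point touches the BMI primary outcome.

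**What to change.** 1. Delete the statements that events and hospitalizations cannot be related to the intervention. Reconcile the Safety section with the Background and Intervention group sections, and with the sentence after Table 1 on what could end the study.
2. Assess the relatedness of recorded hospitalizations case by case and report them by arm.
3. Base any between-arm hospitalization table on the 6- and 12-month visits only. Use information from calls for narratives. State that the planned rehabilitation stay is not counted.
4. At visits still to come, ask both arms the same structured question on hospitalizations, falls or injuries, and events during exercise. State in the report that these data are incomplete for participants who had already passed those visits.

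Cost: a protocol amendment, a short form at existing visits, some data entry and the relatedness review. Items 1 to 3 can be applied to hospitalizations already recorded, provided the source (visit or call) was kept; item 4 cannot be applied retrospectively.

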## Discussion

The S&F for KTx trial is a large randomized controlled study investigating the role of physical activity and nutritional support during the waiting period for a kidney transplant. It has been scientifically established that cardiovascular risk is the most common cause of death among dialysis patients [39] and that more than half of all patients who receive a kidney transplant are considered frail [7]. Additionally, physical inactivity is particularly pronounced in dialysis patients [40] and represents a significant risk factor for a decline in physical performance and a loss of muscle mass. Although several studies have demonstrated that exercise interventions during dialysis or home exercise programs can optimize body composition and improve physical performance [17, 41–43], widespread implementation has not yet been achieved. This is due to various barriers, including intrinsic factors such as fatigue, frailty, anxiety, or depression, and extrinsic factors such as insufficient support from family or the dialysis center [44].

In terms of nutrition, many patients suffer from either malnutrition [22], particularly protein deficiency, or are significantly overweight [45]. Several studies indicate that an adjusted diet can reduce cardiovascular risk [46, 47] and, in conjunction with physical exercise, can optimize body composition and physical performance [48]. Individual support with regular check-ups is necessary to maintain high adherence. Our study aims to address this gap in support and gather data on whether a centralized point of contact during preparation for transplantation can achieve the positive effects of exercise and optimized nutrition through personalized recommendations and regular monitoring.

Severe obesity leads to a significantly increased risk of wound infections, dehiscence, incisional hernias, delayed graft function, and longer hospital stays after transplantation. Moreover, transplant survival is reduced in individuals with a BMI greater than 35 kg/m^2^ [10]. Conversely, being underweight is also a risk factor for increased mortality. Another factor that predicts poorer outcomes after transplantation is frailty. It increases the length of hospital stay and increases the risk of delayed graft function, mortality, and early hospital readmission [49–51]. Therefore, it is important to optimize body composition and physical performance prior to transplantation.

## Conclusions

In summary, our study aimed to assess the effects of individualized and interdisciplinary care prior to kidney transplantation on physical health. The results will help determine whether such care is beneficial for patients on the waiting list and whether it can optimize body composition and physical performance.

The study results will be published in a peer-reviewed journal article upon completion of data collection, regardless of the outcome. The publication process is intended to be as expedited as possible, with an anticipated duration of 3–4 months following the completion of data collection.

In addition to publication in a journal, the results and interim findings will be presented to professionals at scientific conferences, as well as to the general public at patient information events and on the project website. There are no publication restrictions imposed by the sponsor or other stakeholders.

## Data Availability

The study team at the University Hospital Erlangen has full access to the datasets. The data will be pseudonymized in a database (RedCap) and made available to the relevant personnel within the University Hospital Erlangen, including the statistician responsible for the analysis.
